## Abstract

**Introduction:**

Significant advances in systemic therapy have improved survival for patients with advanced-stage non-small cell lung cancer (NSCLC). However, the present treatment strategies and dose-fractionation for high-dose palliative radiotherapy (RT) are based on trials from the 1990s, when RT planning was simple with less precise delivery. Contemporary lung RT uses 4D-CT, volumetric modulated arc radiotherapy, aided by online verification using cone beam CT, which enables greater accuracy and better target volume coverage, while reducing doses to normal organs at risk. The Shortened High-dose Palliative Radiotherapy for Lung Cancer study aims to evaluate the safety and feasibility of reducing the number of RT fractions and RT duration, using contemporary planning, verification and delivery techniques.

**Methods and analysis:**

This single-arm, multicentre, phase-II study will test the shortened hypofractionated accelerated palliative RT regimen of 30 Gy in 6 alternate-day fractions, with strict normal tissue dose constraints. We aim to recruit 37 patients across 4 sites within the West Midlands. Quality assurance for the RT is supported by the Radiotherapy Trials Quality Assurance Group (RTTQA). Patients with locally advanced or metastatic NSCLC, who are candidates for high-dose palliative RT, before or after first-line systemic therapy, are eligible for recruitment. The primary objective of this study is to assess the safety of the proposed dose-fractionation. Secondary objectives include evaluating toxicity profiles, patient-reported outcome measures, time to progression, feasibility and the National Health Service cost-saving.

**Ethics and dissemination:**

This study is conducted in accordance with the International Council for Harmonisation Good Clinical Practice (ICH GCP) guidelines and all applicable regulatory frameworks, including, but not limited to, the UK policy framework for health and social care research, as well as the Health Research Authority and Health and Care Research Wales regulations. Approval for the study was granted on 18 April 2024 (IRAS project ID: 332998; REC reference: 24/WM/0032). The chief investigator is responsible for obtaining informed consent from participants. Any individual delegated this responsibility is thoroughly authorised, trained and competent to conduct the informed consent process. On completion of the trial, the results will be shared with participants in a plain language summary and will be submitted for publication in a peer-reviewed journal. If successful, this study will inform a phase III randomised controlled trial to assess efficacy. For updates on the study, visit the study web page (https://research.mededcoventry.org/About-Us/Meet-The-Team/TMU/Ship-Rt).

**Trial registration number:**

NCT06483308.

Strengths and limitations of this studyInclusion and exclusion criteria were peer reviewed by patient and public involvement groups and the National Cancer Research Institute (NCRI) lung-Clinical Studies Group and tightened to make them relevant to the real-world patient population, allowing for rigorous hypothesis testing in a representative sample population.The primary endpoint is valid, reproducible, relevant to the target population and responsive to the intervention being studied.Simons’s two-stage design is a simple, ethical and efficient adaptive design, with planned interim analysis and clear criteria for stopping or progressing to the next stage; this design is best suited to our phase II oncology trial, where the primary endpoint for each participant is obtained within 4 weeks of their completing radiotherapy.The patient population is prone to high rates of patient loss or attrition from disease progression or death; therefore, our sample size allows for a 15% drop-out rate.

## Introduction

 Non-small cell lung cancer (NSCLC) is a leading cause of cancer-related deaths in the UK and worldwide.^1^,^4^ About 48 000 patients in the UK were diagnosed with lung cancer in 2017. About half of all patients with NSCLC present with metastatic disease.^3^,^5^

Treatment for stage IV NSCLC is aimed at maintaining or improving quality of life by controlling symptoms and prolonging survival. These patients are not curable due to the presence of metastases^6^ and have a 1-year survival of under 20% and a 5-year survival of about 3%.^4^ Advances in systemic therapy have resulted in survival improvement,^7^,^13^ leading to significant expansion in use of targeted therapy using tyrosine kinase inhibitors, immunotherapy, chemotherapy and combination treatments.^13^ Radiotherapy (RT) is used for about 30% of patients with stage IV NSCLC, for local control and symptomatic metastases, either at diagnosis or on disease progression after systemic therapy.^5^ Palliative thoracic RT is also used for patients who are unresponsive to systemic therapy or patients unsuitable for systemic therapy.^14^ High-dose palliative radiotherapy using 30–39 Gy in 10–13 fractions is recommended by the Royal College of Radiologists (2020) for patients with Eastern Cooperative Oncology Group Performance Status 0–2 (online supplemental appendix 4) who are likely suitable for multiple lines of systemic therapy.^15^ The most widely used regimen across the UK is 36 Gy in 12 fractions over 16 days, supported by randomised controlled trial (RCT) evidence from the 1990s, when radiotherapy techniques were simple and less precise.^16^

Clinically relevant organs at risk for palliative thoracic RT are the oesophagus, normal lung tissue and spinal cord. Within the Cochrane review (2015), radiation-related oesophagitis was reported in 8 out of 14 studies (1301 patients) either as patient-reported or physician-assessed toxicity.^17^ The mean rate of grade 3–4 oesophagitis was reported as 25.7% in the intervention groups (that used more fractions) and 22.3% within the control groups (using fewer fractions). Radiation pneumonitis was graded or reported in only 3 out of 14 trials (533 patients) included in the meta-analysis, with the mean reporting rate of 3.9% in the control groups and 2.4% in the intervention group.^17^ The spinal cord remains an organ of concern because of the rare but serious late complication of radiation myelopathy (RM), that was reported by the Medical Research Council Lung Cancer Working Party (MRC-LCWP) in 1996.^18^ The pooled data on 1048 patients from three RCTs conducted by the MRC-LCWP was analysed, and RM was reported in five patients treated with either 17 Gy in 2 fractions (1 week apart) or 39 Gy in 13 fractions (5 fractions/week).^19^ The median survival after palliative RT ranges from 6.2 to 9 months^20^ and 1-year survival was reported as 39%.^17 18^ More recently, 30-day mortality rates have been reported as 9% in a large retrospective single-centre study and about 14% in a large population-based study.^20 21^

The aim of the present study is to investigate the safety and feasibility of reducing the number of rt fractions and the treatment duration, compared with the current standard of care (36 Gy in 12 fractions over 16 days), by using 30 Gy in 6 fractions over 12 days (figure 1), provided the well-defined dose and biologically effective dose (BED) constraints are achievable.

**Figure 1 F1:**
[figure not shown]
A diagram to depict the differences between the standard of care (top row) and the study regimen (bottom row).

## Methods and analysis

The proposed regimen of 30 Gy in 6 alternate-day fractions is comparable to the current standard treatment for tumour control, with similar BED and equivalent dose in 2 Gy fractions.^22^,^25^ From established models for effects of radiation, the proposed regimen should have similar efficacy for tumour control, although this needs to be tested in a phase III RCT, once the regimen is shown to be safe and feasible.^22^,^24^ High-dose palliative RT should be short and sharp and enable appropriate patients to move promptly onto definitive systemic therapy. A 12-fraction, 16-day radiotherapy regimen seems inappropriate when 9%–14% of patients die within 30 days and survival is limited.^20^ With advances in RT planning, verification and delivery techniques, it may be possible to safely treat patients with an adequate dose of palliative RT in fewer fractions, as demonstrated in a recent planning study.^25^ It is possible to keep doses to normal tissues and organs within tolerance by carefully adhering to the established dose constraints during planning and robust verification before delivery.

### Objectives

#### Primary objective

To assess the safety of reducing the number of radiotherapy fractions to 30 Gy in 6 alternate-day fractions over 12 days from the current standard of care by using advanced radiotherapy planning, verification and delivery techniques.

*Hypothesis:* With advances in RT planning, verification and delivery techniques, it is possible to safely treat patients with an adequate dose of palliative radiation in fewer fractions. It is possible to keep doses to normal tissues and organs within tolerance by carefully adhering to the established dose constraints during planning and robust verification before delivery.

#### Secondary objectives

To monitor the overall toxicity profile, including cough, dyspnoea and pneumonitis using CTCAE version 4.03.To assess the feasibility of recruiting patients and treating them in a timely manner while maintaining necessary gaps and washout periods.To assess the time to progression (TTP).To explore the trend with patient-reported outcome measures (PROMS) for quality of life.To assess the cost savings from the proposed treatment.To assess the proposed treatment acceptability to patients and the feasibility to carry it out.

### Patient and public involvement

Through the Patient and Public Research Advisory Group at the UHCW Coventry, we presented the research idea and proposal to a group of patient representatives. Their feedback informed the study’s design and acceptability. Subsequently, we have appointed a patient representative to the study management group. Formal input was obtained from this patient representative and used for all patient-facing literature. They will stay on the trial management group (TMG) for the duration of this study and will help monitor the conduct and progress of this study. Their involvement has been valuable in establishing the database, choice of data fields and outcomes collected, in policies concerning the database, analysis of data and in the proposed dissemination of results.

### Trial design and setting

Shortened High-dose Palliative Radiotherapy for Lung Cancer (SHiP-Rt) is a phase II prospective, single-arm study with a Simon two-stage optimal design (including safety and feasibility). This is a multicentre study, managed by the TMU at UHCW Coventry. The other recruiting sites are University Hospitals Birmingham NHS Trust and The Shrewsbury and Telford Hospital NHS Trust. University Hospitals of North Midlands NHS Trust is waiting to open. A comprehensive table of roles and responsibilities of the individuals involved is included in online supplemental file. Participating centres have access to contemporary radiotherapy techniques as described in the Radiotherapy Protocol (online supplemental file). All participating sites are recruiting, treating and continuing care for study patients as per the protocol and contemporary guidelines. Professionals looking after patients recruited within this study are working within their scope of practice. Participant populations are identified from either the multi-disciplinary team (MDT) or the oncology clinic.

### Eligibility criteria

Patients with locally advanced or metastatic NSCLC, where high-dose palliative radiotherapy (typically 36 Gy in 12 fractions) is being considered for local control or symptomatic metastases, either upfront prior to systemic therapy, or on disease progression after systemic therapy. Those identified at the respective MDT meetings and oncology clinics, after histological diagnosis and staging investigations are complete.

#### Inclusion criteria

All of the following inclusion criteria must be satisfied:

Age ≥18.Patient has locally advanced (stage IIIB or IIIC) or metastatic (stage IV) NSCLC.Patient is treatment naïve or had limited progression after first-line systemic therapy (using chemotherapy, immunotherapy or targeted therapy).Patient is suitable for high-dose palliative RT (36 Gy in 12 fractions or 39 Gy in 13 fractions).Obtained written informed consent for the SHiP-Rt study.Patients receiving RT after first-line systemic therapy must have a wash-out period of at least 3 weeks (ie, 3–4 weeks).Treatment-naïve patients should be able to proceed to definitive systemic therapy without undue delay, that is, within 3–4 weeks.

#### Exclusion criteria

The presence of any of the following criteria would render the patient ineligible for this study:

Contraindication for thoracic RT.Requiring lung RT after second-line systemic therapy for NSCLC.Has more than one cancer that requires active treatment.On cytotoxic treatment for rheumatoid arthritis or connective tissue disorders.Poor life expectancy, likely less than 6 months.Patients with difficulty regarding compliance with the study treatment or follow-up.Previous radiotherapy to the same area.

### Outcomes

#### Primary outcome

The proportion of patients successfully completing treatment without reporting grade 3–4 oesophagitis, within 4 weeks of completing RT (using CTCAE version 4.03), out of all patients starting treatment in this study. The time points at which the toxicity will be assessed and recorded within 12 months of completion of radiotherapy are described in the schedule of events.

#### Secondary outcomes

Toxicity assessments for common acute and late toxicity using CTCAE version 4.03.Assess the feasibility of recruiting patients (number of patients screened, eligible, recruited and withdrawn) and treating them in a timely manner while maintaining necessary gaps and washout periods. Record the time at which systemic therapy was initiated from recruitment and from the end of radiotherapy.TTP—documentation of the time at which disease progression occurs from the end of radiotherapy.PROMS responses using EORTC QLQ-C30 and QLQ-LC13 at baseline and timepoints as described in the schedule of events.Calculations of cost savings from the proposed treatment regimen.The acceptability of the treatment to participants by recording how many participants participate in the study versus how many consent versus how many complete treatment.

### Sample size

The primary endpoint is the proportion of patients successfully completing treatment without reporting grade 3–4 oesophagitis, using CTCAE version 4.03 out of all patients starting treatment within this study.

The study regimen will be considered as:

Feasible, if >70% patients complete treatment and do NOT report grade 3–4 oesophagitis.Not feasible, if <45% patients complete treatment and do NOT report grade 3–4 oesophagitis.

Simon’s two-stage design (Simon, 1989) ^26^ has been adopted. The null hypothesis that the true response rate is 45% will be tested against a one-sided alternative. Recruiting 37 patients will allow detection of the rate being ≤45% or ≥70%, with one-sided 5% significance and 85% power. This calculated sample size allows for a 15% attrition rate.

#### Stage 1 analysis

Patients will be accrued until 11 patients have primary endpoint information available. If there are five or fewer patients who completed treatment and did NOT report grade 3–4 oesophagitis (ie, six or more who either failed to complete treatment, or reported grade 3–4 oesophagitis), the study will be stopped early for futility. Otherwise, it will continue to recruit.

#### Stage 2 analysis

Additional patients will be accrued until a minimum of 31 patients have primary endpoint information available is reached (anticipated to be attained with 37 patients recruited). If 19 patients or more completed treatment and did NOT report grade 3–4 oesophagitis, the null hypothesis will be rejected, and the regimen will be considered feasible.

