### Trial status

The study is currently running under protocol version 1.2 (dated 19 November 2025). Recruitment started in November 2024, and the study remains on track for completion in March 2027. To date, we have recruited 23 patients,^27^ and the stage 1 analysis concluded that study recruitment should continue to the full 37 patient target. For updates on the study, please visit the study web page (https://research.mededcoventry.org/About-Us/Meet-The-Team/TMU/Ship-Rt).

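### The stage 2 cut-off of 19 successes gives the stated 5% error only at exactly 31 evaluable patients, but 31 is a minimum and recruitment runs to 37

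*Protocol article*

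**What the plan says.** The Trial design and setting section describes a "single-arm study with a Simon two-stage optimal design". The Sample size section sets the null ("The null hypothesis that the true response rate is 45% will be tested against a one-sided alternative") and the operating characteristics: "Recruiting 37 patients will allow detection of the rate being ≤45% or ≥70%, with one-sided 5% significance and 85% power". It adds: "This calculated sample size allows for a 15% attrition rate".

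Under Stage 1 analysis, the trial stops for futility if 5 or fewer of 11 evaluable patients succeed. A success is a patient who completes treatment and reports no grade 3–4 oesophagitis.

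Under Stage 2 analysis: "Additional patients will be accrued until a minimum of 31 patients have primary endpoint information available", with 37 recruits expected to be enough to get there. The rejection rule that follows is a bare count: "If 19 patients or more completed treatment" without grade 3–4 oesophagitis, the null is rejected.

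Two other sections bear on the denominator. Statistical methods defines the endpoint population as patients who start treatment and supply endpoint information, sets no upper limit on it, and compares the result with the cut-offs already specified. Trial status reports that the stage 1 analysis concluded that "study recruitment should continue to the full 37 patient target".

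**The concern.** A Simon cut-off is calibrated to one final sample size. Here the count is fixed and the denominator is open at the top. With 31 evaluable patients, 19 successes is an observed rate of 19/31 = 61.3%. With 37 it is 19/37 = 51.4%, much nearer the 45% null. Each evaluable patient beyond 31 is one more chance to reach 19, so any departure from the stated 5% is upward, towards declaring feasible a regimen whose true success rate is only 45%.

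Stage 2 is the only point at which the null can be rejected, and a success is meant to inform a phase III trial. Stage 1 is done and 23 patients have been recruited, so the wording can still be settled before stage 2 data are seen.

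**Working it through.** **Inputs.** From Sample size: p0 = 0.45, p1 = 0.70, one-sided alpha 0.05, power 0.85, attrition 15%. From Stage 1 analysis: n1 = 11, continue if X1 ≥ 6. From Stage 2 analysis: reject if the total is ≥ 19, with final evaluable n ≥ 31 and 37 recruits expected.

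**Formula.** With X1 ~ Bin(11, p) and X2 ~ Bin(n − 11, p) independent,

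P(reject | p, n) = Σ (x = 6 to 11) P(X1 = x) · P(X2 ≥ 19 − x).

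**Step 1: reproduce the plan.** At n = 31 the sum is 0.0439 for p = 0.45 and 0.8505 for p = 0.70. A full search over two-stage designs with these inputs returns the same optimal design (5/11, reject at ≥ 19/31). Recruitment is 31/0.85 = 36.5, rounded up to 37. The stated design and sample size are therefore correct at 31.

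**Step 2: hold the cut-off at 19 and let n rise.**

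| Evaluable n | 19/n | Type I error (p = 0.45) | Power (p = 0.70) |
|---|---|---|---|
| 31 | 61.3% | 0.0439 | 0.8505 |
| 32 | 59.4% | 0.0607 | 0.8786 |
| 33 | 57.6% | 0.0804 | 0.8966 |
| 34 | 55.9% | 0.1024 | 0.9075 |
| 35 | 54.3% | 0.1260 | 0.9139 |
| 36 | 52.8% | 0.1506 | 0.9176 |
| 37 | 51.4% | 0.1754 | 0.9196 |

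One evaluable patient beyond 31 is enough to exceed 5%.

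**Step 3: weight by how likely each n is.** Assume 37 recruits, each evaluable independently with probability 0.85, so n ~ Bin(37, 0.85) with mean 37 × 0.85 = 31.45.

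- P(n < 31) = 0.315. The plan keeps accruing until 31 are evaluable, so assume these cases are tested at 31, with error 0.0439.
- P(n = 31) = 0.172.
- P(n = 32), …, P(n = 37) = 0.183, 0.157, 0.104, 0.051, 0.016, 0.002. Together these give P(n > 31) = 0.513.

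Average error = (0.315 + 0.172) × 0.0439 + 0.183 × 0.0607 + 0.157 × 0.0804 + 0.104 × 0.1024 + 0.051 × 0.1260 + 0.016 × 0.1506 + 0.002 × 0.1754 ≈ 0.065.

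Conditional on n ≥ 31, the average is 0.075. If attrition were 10% (an assumed value), P(n > 31) is 0.84 and the overall average error is about 0.092.

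**Step 4: cut-offs that restore the level.** Keeping the stage 1 rule, the smallest cut-off with exact error ≤ 0.05 is:

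| Evaluable n | Cut-off | Type I error | Power |
|---|---|---|---|
| 31 | 19 | 0.0439 | 0.851 |
| 32 | 20 | 0.0312 | 0.829 |
| 33 | 20 | 0.0445 | 0.864 |
| 34 | 21 | 0.0320 | 0.846 |
| 35 | 21 | 0.0449 | 0.875 |
| 36 | 22 | 0.0326 | 0.860 |
| 37 | 22 | 0.0451 | 0.883 |

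**The case against.** The strongest reply is that 37 is a recruitment target, not an evaluable number. A reader might infer that the trial will in practice run at a 17.5% error, or reject a true null far more often than 5%. The documents do not support that. At the planned 15% attrition the chance that all 37 are evaluable is about 0.24%, and the average error is about 6.5%. This part of the reply stands, and 17.5% is only the upper limit. It also stands that there is no arithmetic slip, since the design reproduces exactly at 31, and that stage 2 is not the trial's only decision rule, since stage 1 had its own and has been applied.

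A second reply is that the accrual sentence can be read as a stop at the 31st evaluable patient. That reading is weakened by the word minimum, by the uncapped analysis population in Statistical methods, and by the statement in Trial status that recruitment continues to 37.

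A third is that the SAP, which is not shown, may deal with over-accrual. It may. But the article does more than stay silent: it states a fixed count with an open denominator and refers the analysis back to that count. An SAP with a different bound would conflict with the Stage 2 text.

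A fourth is that the percentage and its 95% CI will be reported, so a result such as 19/37 would be visible. That helps the reader but does not change the stated rejection rule.

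**Conclusion.** The point holds. Followed as written, the stage 2 rule exceeds the stated one-sided 5% level whenever 32 or more patients are evaluable. The sizes most likely to matter are 6.1% at 32, 8.0% at 33 and 10.2% at 34. Averaged over independent 15% attrition from 37 recruits, with shortfalls topped up to 31, the error is about 6.5%, and more than 31 are evaluable about half the time.

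The average depends on the attrition assumption; the error at each n does not. Attrition below 15% is plausible, because a patient who starts but does not complete treatment counts as a failure and stays in the denominator. Only patients who never start, or who give no endpoint information, leave it.

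**What to change.** Amend the Stage 2 analysis text, and the SAP if it repeats the rule, before any stage 2 outcome data are seen. Choose one option and state it:

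1. Base the formal test on the first 31 evaluable patients in order of starting treatment, including the 11 from stage 1. Keep the cut-off at 19 and report later patients descriptively. Error stays at 4.4% and power at 85.05%.
2. Test all evaluable patients and replace the single count with cut-offs by final n: 31→19, 32–33→20, 34–35→21, 36–37→22. Error is 0.031 to 0.045 and power 82.9% to 88.3%.

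The cost is wording only, with no extra patients. Option 2 uses all the data, but power falls slightly under 85% at n = 32 (82.9%) and n = 34 (84.6%). Option 1 keeps the stated design exactly but leaves later patients out of the formal test. Leaving the choice until the data are in would allow the denominator to be chosen after the fact.

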### Data monitoring

The TMG meets on a monthly basis to discuss serious adverse events, quality of data entered, progress of the trial, protocol adherence, any proposed protocol amendments and any other problems.

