### Interim analysis

The Simon’s two-stage design has been adopted for this study and analysis will be undertaken after 11 patients have primary endpoint information available, with the study being stopped early for futility if there are 5 or fewer patients who completed treatment and did NOT report grade 3–4 oesophagitis at this stage (ie, 6 or more who either failed to complete treatment, or reported grade 3–4 oesophagitis). Otherwise, recruitment will continue. This analysis will be performed by the study statistician based at Warwick Clinical Trials Unit and shared with the study’s oversight committee for the decision to be made regarding the continuation with stage 2.

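### Stage 2 has no stop for when 19 successes in 31 can no longer be reached; fixing the analysis at 31 and stopping recruitment at the 13th failure costs no alpha or power

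*Protocol article*

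**What the plan says.** The protocol article describes a "single-arm study with a Simon two-stage optimal design". A success is a patient who completes treatment without grade 3–4 oesophagitis. A failure is non-completion or grade 3–4 oesophagitis.

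- **Stage 1 analysis:** "Patients will be accrued until 11 patients have primary endpoint information available". The trial stops for futility with five or fewer successes.
- **Interim analysis:** the same rule is repeated, followed by "Otherwise, recruitment will continue". The oversight committee takes the decision.
- **Stage 2 analysis:** "Additional patients will be accrued until a minimum of 31 patients have primary endpoint information available is reached". The null is rejected with 19 or more successes. Reaching 31 is expected to take 37 recruits.
- **Data monitoring:** "The TMG meets on a monthly basis to discuss serious adverse events", together with data quality, progress, adherence and amendments. No numerical trigger on the primary endpoint is given.
- **Trial status:** stage 1 has been passed, 23 patients are recruited and recruitment continues towards 37.

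**The concern.** The primary objective is safety, and the article presents the design as ethical and efficient, with clear stopping criteria. After the look at 11 patients, however, nothing links accumulating failures to continued recruitment. If 31 patients are analysed and 19 must succeed, at most 12 may fail. Once a 13th has failed, the trial cannot meet its success criterion, yet the text still calls for accrual to at least 31. At stake are the patients enrolled after the primary question has been settled.

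The stop can be added without the usual price of an extra look, because it acts only when the result of the test is already determined. That holds only if the final number analysed is fixed, and the word minimum in the stage 2 rule leaves it open.

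**Working it through.** **Inputs.** p0 = 0.45, p1 = 0.70, one-sided alpha 5%, power 85%, attrition 15% (Sample size); n1 = 11, stop if 5 or fewer successes (Stage 1 analysis); n = 31, reject if 19 or more successes (Stage 2 analysis).

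**1. Reproduce the design.** With X1 ~ Bin(11, p) and X2 ~ Bin(20, p),

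P(reject) = Σ (x = 6 to 11) P(X1 = x) · P(X2 ≥ 19 − x).

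- p = 0.45: 0.1931×0.0580 + 0.1128×0.1308 + 0.0462×0.2493 + 0.0126×0.4086 + 0.0021×0.5857 + 0.0002×0.7480 = **0.0439**
- p = 0.70: 0.1321×0.7723 + 0.2201×0.8867 + 0.2568×0.9520 + 0.1998×0.9829 + 0.0932×0.9949 + 0.0198×0.9987 = **0.8505**

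A full search returns 5/11 and 18/31 as the optimal design. Attrition: 31/0.85 = 36.5, rounded up to 37. The plan's figures stand.

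**2. The decisive failure count.** With n = 31, 13 failures leave at most 31 − 13 = 18 successes, one short of 19. Stopping there removes only paths that could not reject, so alpha stays 0.0439 and power 0.8505. A stop at the 12th failure would not be neutral (alpha 0.0302, power 0.8084). A trial that passes stage 1 has at most 11 − 6 = 5 failures, so the 13th can come no earlier than patient 11 + 8 = 19, leaving 31 − 19 = 12 untreated at most.

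**3. Why n must be fixed.** With n evaluable and the bar held at 19, rejection becomes impossible at failure n − 18.

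| n evaluable | decisive failure | alpha, bar 19 | power, bar 19 |
|---|---|---|---|
| 31 | 13th | 0.0439 | 0.8505 |
| 32 | 14th | 0.0607 | 0.8786 |
| 34 | 16th | 0.1024 | 0.9075 |
| 37 | 19th | 0.1754 | 0.9196 |

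At n = 34, a stop at the 13th failure would itself change the test, to alpha 0.0218 and power 0.8047.

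**4. Size of the saving (n = 31).** An exact patient-by-patient recursion applies the stage 1 rule and then stops at the 13th failure. The stopping chance and the mean spared are conditional on passing stage 1. The last two columns assume k patients already in treatment or follow-up when the 13th failure becomes known; the article gives no such figure.

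| True success rate | Passes stage 1 | Stops before patient 31 | Mean spared, k = 0 | k = 2 | k = 4 |
|---|---|---|---|---|---|
| 35% | 14.9% | 97.48% | 7.1 | 5.1 | 3.3 |
| 45% | 36.7% | 83.46% | 4.6 | 3.0 | 1.7 |
| 55% | 63.3% | 50.14% | 2.1 | 1.2 | 0.5 |
| 60% | 75.3% | 30.99% | 1.1 | 0.6 | 0.2 |
| 70% | 92.2% | 5.78% | 0.2 | 0.1 | 0.0 |

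Unconditionally, expected N falls from 18.34 to 16.65 at 45% and from 29.44 to 29.28 at 70%.

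**5. Effect on the reported proportion.** The same recursion gives the mean of successes/N among trials passing stage 1, without and with the stop: 58.2% and 57.8% at a true rate of 55%; 62.3% and 61.9% at 60%; 70.8% and 70.7% at 70%. At these rates the stop pulls the estimate down by less than half a point. At 45% the means are 50.6% and 50.7%, and at 35% they are 43.3% and 45.1%, because the favourable stage 1 result then carries more weight.

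**The case against.** The strongest reply is that nothing here is wrong. A Simon design without stage 2 curtailment is standard, its numbers reproduce exactly and it has the single interim look it claims. That stands: this is an improvement, not the correction of an error.

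Three stronger readings are tempting, and the documents do not support them.

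- **That the 13th failure settles the matter as the text is written.** It does so only for n = 31. Under an open minimum with a fixed bar of 19, the decisive count moves with n.
- **That the regimen would be certain to be declared not feasible.** The Sample size section reserves that label for a rate below 45%. Eighteen of 31 is 58%, between the two stated zones. Missing 19 means the null is not rejected and nothing more.
- **That later patients would be treated without purpose, or that 13 failures are 13 toxicities.** Later patients still inform toxicity, PROMS, TTP, feasibility and cost. Failure includes non-completion for any reason, in a population the article calls prone to progression and death.

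It is also fair to say that the saving is small where the regimen works, that patients already in treatment or follow-up reduce it, and that the poor scenarios seldom pass stage 1 (14.9% at 35%). Oversight exists, through monthly review by the trial management group and an oversight committee. The full protocol or SAP, not shown, may hold further stopping provisions. None of this alters the fact that the article states the stage 2 accrual rule without exception, or that the added stop is neutral at n = 31.

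**Conclusion.** The point holds as an inexpensive improvement to a sound design. Once the primary analysis is fixed at 31 evaluable patients, stopping recruitment at the 13th failure leaves alpha at 0.0439 and power at 0.8505. Given stage 1 is passed, the mean saving runs from 7.1 patients at a true rate of 35% to 0.2 at 70%, before allowing for those already in treatment or follow-up.

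The figures assume independent patients with a common success rate, exactly 31 analysed, and a rule in force from patient 12. With 23 already recruited and the current failure count not reported, the saving still available to this trial cannot be calculated from the article. Fixing n is worth doing whether or not the stop is adopted, because it protects the stated 5% significance level.

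**What to change.** 1. Fix the primary analysis at the first 31 evaluable patients, taken in order of starting treatment. Report any further evaluable patients descriptively.
2. Add to stage 2 that the oversight committee receives a running count of primary-endpoint failures, and that recruitment stops once 13 are recorded among those 31, because the null can no longer be rejected. If another n and cut-off c are planned, the count is n − c + 1. The rule concerns recruitment only, not the care of patients already started.
3. State that reaching 13 means the null is not rejected, and report failures split into grade 3–4 oesophagitis and non-completion by reason.
4. If the stop is triggered, use a confidence interval for the primary proportion that allows for the stopping rule.

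The cost is a short amendment and a regular tally of data already collected. If the stop is triggered, there are fewer data for toxicity, PROMS and TTP. The reported proportion is then less precise and, at true rates of 55% and above, biased slightly downward relative to running on to 31.
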